### Participants

#### Inclusion criteria

Participants must meet the following conditions: (1) the diagnostic criteria of Parkinson’s Disease in China (2016) (5), Hoehn Yahr grade of I–III; (2) presence of mild cognitive impairment (MCI), not demented: MoCA score between 21 and 26 points (30); (3) aged between 60 and 75 years; (4) stable disease at least 3 months before randomization (confirmed to have no acute aggravation and related drug changes); (5) can cooperate and complete the relevant evaluations and tests; and (6) willing to provide written informed consent.

#### Exclusion criteria

Exclusion criteria are as follows: (1) patients with severe bone, joint, and muscle diseases, as well as heart, liver, kidney, and other serious life-threatening diseases or mental illness; (2) patients with severe language, visual, and hearing impairment; (3) patients who have suffered from other severe diseases in the past year which may affect motor ability or cognitive function; (4) patients who have experience doing TCEs in the past; and (5) patients who are participating in other clinical studies.

### Randomization and blinding

Participants will be assigned randomly to one of the three groups using a random number table generated by SPSS V.24.0 to minimize bias. A designated researcher who will not be involved in any other aspect of the study will be responsible for implementing the randomization scheme. Random numbers will be placed in opaque envelopes, and only the designated researcher will know the assigned sequence. The therapists will know the treatment plan for each group, the evaluators and data analysts will be blinded until statistical analyses are completed. Participants will only be informed of their treatment methods in their respective groups and will not be aware of the treatment plans of other participants. All researchers will undergo training before the trial to successfully implement randomization and blinding.

### Baseline assessment

Before the outset of the study, we will gather comprehensive descriptive information from all participants, including general data (name, gender, age, etc.), clinical symptoms (symptom screening for PD and MCI), vital signs (pulse, breathing, blood pressure, etc.). This information will allow us to compare the baseline characteristics of the three groups involved in the study. To further supplement this data, we will conduct the first clinical-scale evaluation and acquire cerebral blood oxygen signals from the prefrontal cerebral and sensorimotor cortex during the baseline assessment. Together, this data will provide valuable insights into the study’s starting point and help us draw more accurate conclusions from the research.

### Intervention

All participants will receive monthly health education as part of the intervention. Each session will be 60 min, covering topics such as the concept, risk factors, and self-management of PD. The intervention will be conducted by licensed therapists with at least 5 years of experience. The control group will be instructed to maintain their existing daily habits. The Yijinjing exercise group will be trained by an expert in TCEs and receive guidance throughout the 12-week program, while the brisk walking group will receive treatment from a professional technician. The intervention will be conducted once a day, 3 days a week (Monday, Wednesday, and Friday) for 12 weeks. Participants will be allowed to continue their current drug treatment as long as it benefits their condition.

### Yijinjing exercise group

Participants in this group will engage in a 12-week Yijinjing exercise program consisting of 12 movements. These movements adhere to the standards established by the General Administration of Sport of China^1^ and will be practiced alongside background music. A picture of the specific movements is available in a previously published article (31). Each exercise session will last for 40 min, divided into 5 min of muscle stretching as preparation, 30 min of Yijinjing exercise, and 5 min of free walking to cool down. The same therapist will supervise the entire exercise process for all participants. Participants who cannot complete the movements independently can receive assistance from the therapist.

### Brisk walking group

Participants in this group will receive brisk walking training. Adopting a moderate intensity aerobic exercise method, with a dedicated therapist supervising the entire exercise process for all participants. 40 min each exercise session, consisting of a 5 min warm-up, 30 min of walking training and a 5 min cool-down. The heart rate during walking should be 50%–60% maximum heart rate (220—age). Monitored by sport watches in heart rate, distance, speed, and walking quality (32).

### Follow-up

After 12 weeks of treatment, participants will undergo a 1-month follow-up period. As they will not have access to equipment and professionals during this period, we will not require them to continue with the corresponding treatment but instead encourage them to resume their daily routine. After the 1-month follow-up, all participants will be required to return to the hospital to reassess of the results.

### Outcome measurements

This research will assess the primary and secondary outcomes and the cerebral blood oxygen signal level by collecting data at baseline, after 12 weeks of treatment, and again at the end of a 1-month follow-up period. To ensure impartiality, all outcome assessments will be conducted by an experienced therapist who is unaware of the randomization of the participants.

#### Primary outcome

Cognitive and motor functions will be measured using the MoCA and UPDRS assessments, respectively. The MoCA evaluates 8 aspects of the cognitive domain, including visual space and execution, naming, memory, attention, language, abstraction, delayed recall, and orientation (33). With a total score is 30, a score of ≥26 indicates no cognitive impairment. Alternate Chinese versions 7.1 and 7.2 will be used to minimize the learning effect before and after the treatment. On the other hand, the UPDRS is the most widely used, well validated clinical rating scale for PD, UPDRS-III is the motor section of UPDRS, through 18 tasks, each scored from 0 to 4, with a maximum score of 72 (34).

#### Secondary outcomes

Secondary outcomes of this study include balance function, executive function in specific cognitive areas, walking function, sleep, and quality of life.

##### Balance function

Berg Balance Scale (BBS) measures static and dynamic balance abilities through 14 tasks, each scored from 0 to 4, with a maximum score of 56 (35).

##### Executive function

Executive function will be assessed using the Trail Making Test (TMT) (36), which consists of two parts, A and B. Part A requires participants to connect irregularly scattered numbers from 1 to 25 as quickly and accurately as possible. Part B includes numbers and letters, which are required to be connected in the order in which numbers and letters cross, such as 1 connected to A, A connected to 2, 2 connected to B, etc. The time it takes to complete and the number of errors across both parts will be recorded.

##### Walking function

The walking function will be assessed using the 6-Minute Walk Test (6MWT) (37), which requires participants to walk back and forth as much as they can over the course of 6 min. Participants are not allowed to talk while walking or run and jump. Researchers will follow participants to protect them and record their total walking distance.

##### Sleep

Sleep will be assessed using the Pittsburgh Sleep Quality Index (PSQI) (38). Participants will complete a self-assessment, including 7 parts consisting of 18 self-assessment items, with scores ranging from 0 to 21. In general, the higher the score, the worse the sleep quality.

##### Quality of life

The Parkinson’s Disease Questionnaire 39 (PDQ-39) will assess the quality of life (39). PDQ-39 consists of 39 items, assessing 8 dimensions of physical activity, daily life behavior, mental health, humiliation, social support, cognition, communication, and physical discomfort. The score ranges from 0 to 156. The higher the score, the lower the quality of life.

#### Exploratory outcomes

The near-infrared brain functional imaging system (NirSmartII-3000A, Danyang HuiChuang Medical Equipment Co., Ltd., Danyang, China) will be operated by trained professionals to capture cerebral blood oxygen signals in the prefrontal cerebral and sensorimotor cortex. The device features 16 emission and 24 detector probes, with 64 channels available. To ensure consistency, participants will wear an A-type optical fiber cap configured by the instrument and their prefrontal and sensorimotor region will be located according to the 10–20 system marker points. Shown in Figure 2. To elicit task-based responses, participants will be asked to perform three tasks.

**Task 1:** Participants wore the fNIRS detection cap and sat in a chair. They were instructed to keep still with their eyes closed, relax their mind, and minimize their movement for at least 8 min for the resting-state recording (40) (Figure 3).**Task 2:** the verbal fluency task (VFT): Participants wore the fNIRS detection cap and sat in a chair. The task time is about 160 s. The first 30s and the last 70s of the experiment are used to collect the resting-state signal of the participants. During these two stages, the participants are required to count from one to five repeatedly. During the second stage, the participants performed VFT of three consecutive word-generating tasks, each of which lasted 20 s (41) (Figure 3).**Task 3:** Walking while performing cognitive task (WCT): Participants will be asked to walk on a 30-meter walkway. They will be first provided with 2 familiarization trials of the walking condition to become accustomed to walking with the fNIRS backpack. The task time is 75 s. Participants stand quietly at the beginning of the corridor for the first 15 s of the experiment, and then walk back and forth at a comfortable walking speed along a straight distance of 30 meters for the last 60 s while subtracting 3 from an initial three-digit number (between 900 and 1,000) serially and speaking out each calculated number as quickly as possible. Repeat 3 times, with a 60 s seat rest between each session (Figure 3).

**Figure 2 fig2:**
[figure not shown]
Configuration of fNIRS channels.

**Figure 3 fig3:**
[figure not shown]
Three tasks for fNIRS.

The fNIRS data will be analyzed using the Homer2 package in MATLAB and customized MATLAB-based script (42).

##### Safety

All adverse events that occur during the trial will be documented, regardless of whether they are related to the study. The ethics committee will be promptly notified if any severe adverse events arise. A clinician from the Department of Neurology of the Second Rehabilitation Hospital of Shanghai will provide the necessary treatment. The ethics committee will evaluate the correlation between the adverse events and the trial intervention and will determine whether the participant can continue the trial, which will be accurately recorded in the case report form (CRF).

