**Methods:**

This is a single-center randomized controlled trial in which 96 eligible PD patients will be randomly assigned to receive either Yijinjing exercise group or brisk walking group or control group in a ratio of 1:1:1. Interventions (Yijinjing exercise or brisk walking training, 40 min per session) will be provided in 3 sessions per week (Monday, Wednesday, Friday) for 12 weeks, with a total of 36 sessions. After the treatment, there will be a 1-month follow-up period. The primary outcomes will be measured using the Montreal Cognitive Assessment (MoCA) and the Unified Parkinson’s Disease Rating Scale motor section (UPDRS-III). Secondary outcomes include balance function, executive function, walking function, sleep quality, and quality of life. Additionally, the prefrontal cerebral and sensorimotor cortex blood oxygen signal level will be collected to explore the underlying mechanisms. All outcomes will be assessed at baseline, at the end of 12 weeks of treatment and after an additional 1-month follow-up period.

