##### Quality control

The trial study will establish a unique quality control group in order to train participants in recruitment, assessment, treatment, and data analysis so as to minimize bias. Throughout the trial, the quality control group will strictly record medication taken by participants and be responsible for communicating with participants and monthly health education. The intervention group will each assign a designated therapist to carry out one-on-one free treatment throughout the trial to reduce the differences in therapeutic effects between therapists. The above measures will assist in improving participant compliance and reduce the loss rate of follow-up.

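### Descriptive adverse event counts for either exercise arm against control are at risk of detection bias, because supervised contact differs greatly and no common enquiry is scheduled between week 1 and week 12

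*Protocol article*

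**What the plan says.** All places are in the protocol article.

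- **Safety:** "All adverse events that occur during the trial will be documented, regardless of whether they are related to the study". The section does not say who asks, how, or at which contacts.
- **Abstract, Methods:** the exercise interventions "will be provided in 3 sessions per week (Monday, Wednesday, Friday) for 12 weeks, with a total of 36 sessions", at 40 minutes each.
- **Yijinjing exercise group:** "The same therapist will supervise the entire exercise process for all participants".
- **Brisk walking group:** training is delivered "with a dedicated therapist supervising the entire exercise process for all participants".
- **Intervention:** "The control group will be instructed to maintain their existing daily habits". For all arms, "All participants will receive monthly health education as part of the intervention" and "Each session will be 60 min, covering topics such as the concept, risk factors, and self-management of PD".
- **Table 1:** one adverse event row, not split by arm, is marked at baseline, week 1, week 12 and the 1-month follow-up.
- **Quality control:** a quality control group records medication throughout and will "be responsible for communicating with participants and monthly health education". The frequency of that communication is not given, and it is not limited to particular arms.
- **Statistical analysis:** the methods concern primary and secondary outcomes. No between-arm comparison of adverse events is described.

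**The concern.** Safety promises complete recording in every arm, but the opportunity for an event to be noticed differs greatly by arm. A strain, a dizzy spell or a near-fall in an exercise participant can be seen by the therapist or mentioned at the next session, two or three days later. A control participant with the same event may have to remember it until the next monthly talk, where no adverse event question is planned, or until the week-12 visit.

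If minor events are lost more often in control, the exercise arms will appear to have more of them even when the true rates are equal. The Discussion part of the abstract looks ahead to Yijinjing as a family activity for patients and people at risk, so readers are likely to set its event counts beside those of control whether or not a test is done. The primary and secondary efficacy outcomes are not touched.

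**Working it through.** **1. The plan's own session count.** 3 sessions per week × 12 weeks = 36, as stated in the abstract.

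**2. Contacts common to all arms.** Monthly talks in 12 weeks: 12 / (52/12) = 2.8, taken as 3.

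**3. Planned sessions and talks in the intervention period.**

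| Arm | Supervised sessions | Talks | Contacts | Minutes |
|---|---|---|---|---|
| Yijinjing | 36 | 3 | 39 | 36 × 40 + 3 × 60 = 1620 |
| Brisk walking | 36 | 3 | 39 | 1620 |
| Control | 0 | 3 | 3 | 3 × 60 = 180 |

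Either exercise arm against control: 39/3 = 13 in contacts and 1620/180 = 9 in time. Yijinjing against brisk walking: 1 on both. If the three post-baseline Table 1 points are added as separate contacts, the comparison with control becomes 42 against 6, a ratio of 7.

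**4. What Table 1 fixes.** There are four adverse event time points in every arm. Between week 1 and week 12 lie 11 weeks without a marked enquiry; the exercise arms have 11 × 3 = 33 supervised sessions in that time. The row can be read in two ways.

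- *The marks are the only collection points.* The schedule is then equal but sparse. Counts stay comparable only if events witnessed at sessions are kept apart, yet Safety requires every event to be documented.
- *The marks show a span.* This is plausible, since the intervention rows are also marked only at weeks 1 and 12 although sessions run three times a week. Collection is then continuous and depends on contacts that differ as in step 3.

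Neither reading supplies a rule that makes exercise and control counts comparable. After week 12 no arm has required sessions, so the imbalance belongs to the intervention period.

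**5. How the bias would scale.** With equal true risk, apparent risk ratio = detection in exercise / detection in control. The documents give neither figure. The values below are assumptions, with detection in exercise held at 90%. The expected cases also assume a true risk of 20% and 32 per arm (96/3, from the abstract's total).

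| Detection in control | Apparent ratio | Expected recorded cases, exercise against control |
|---|---|---|
| 90% | 1.00 | 5.8 against 5.8 |
| 70% | 1.29 | 5.8 against 4.5 |
| 50% | 1.80 | 5.8 against 3.2 |
| 30% | 3.00 | 5.8 against 1.9 |

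The table shows direction and scale only. It is not an estimate for this trial.

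**The case against.** The case on the other side has several parts.

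- **The schedule is uniform.** Table 1 gives every arm the same four points, and nothing in the article says that adverse events are collected at exercise sessions. This stands to the extent that capture through the sessions is an inference. It does not remove the risk: an event that a supervising therapist witnesses falls under the promise to document everything, and control has no matching opportunity.
- **Control contact is undercounted.** The quality control group communicates with participants throughout. This also stands in part, so 13 to 1 is a ratio of planned sessions and talks, not of adverse event enquiries. But no frequency is given, and the recording duty named for that group is medication.
- **No safety comparison is planned.** This is correct. Safety is not a listed primary, secondary or exploratory outcome and no test is described, so the matter is one of descriptive reporting.
- **Elicitation detail belongs in the full protocol.** This is fair for the wording of forms. The contact imbalance and the promise covering all arms are, however, both stated in the article, and the point rests on the two together.

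A reader might infer more: that every between-arm safety comparison is biased, that exercise counts will certainly look higher, or that a fall-preventing effect will be masked. The documents do not support these. The two exercise arms have equal contact, equal detection remains possible, and falls are not an outcome of the trial. A reader might also take a range such as 1.6 to 2.7 (80% detection in exercise against 50% to 30% in control) as the expected distortion. Those rates have no source in the documents, and the range leaves out equal capture.

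**Conclusion.** The point holds as a minor one. Adverse event counts for Yijinjing or brisk walking set beside control are at risk of detection bias, and the likely direction is to make exercise look less safe. What the documents establish is the contact imbalance (about 39 planned contacts against 3 over 12 weeks, assuming three monthly talks) and the absence of a marked enquiry between week 1 and week 12. They do not allow the size of the bias to be estimated; it is zero if the common schedule yields equal detection. Yijinjing against brisk walking is not affected by this mechanism, and no planned hypothesis test depends on it.

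**What to change.** At each monthly health-education session, and at the 12-week and 1-month visits, have the quality control group put the same short set of adverse event questions to every participant in all three arms. The blinded assessor should not do this, because answers about exercise sessions could reveal the allocation. Record the source of each event: uniform questions, seen or volunteered at a session, or other contact.

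Report two things side by side:

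1. Events elicited by the uniform questions, as the like-for-like comparison with control.
2. All events, including those seen or volunteered at exercise sessions, labelled by source and with none dropped. An event reported by both routes is counted once here, with both sources noted.

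The second table is needed because leaving out session events could hide the harms most likely to come from the intervention itself.

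The cost is a short form, a few minutes per participant per month, and an extra line in the safety table. The contacts and the group already exist. The source of an event is hard to recover afterwards, so the rule should be in place before data are collected. Some difference may remain, since frequent contact can itself prompt recall, and the report should say so.

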##### Quality control

The trial study will establish a unique quality control group in order to train participants in recruitment, assessment, treatment, and data analysis so as to minimize bias. Throughout the trial, the quality control group will strictly record medication taken by participants and be responsible for communicating with participants and monthly health education. The intervention group will each assign a designated therapist to carry out one-on-one free treatment throughout the trial to reduce the differences in therapeutic effects between therapists. The above measures will assist in improving participant compliance and reduce the loss rate of follow-up.

##### Data management and monitoring

To safeguard participants’ privacy, the evaluator will assign an identification code to each individual, concealing their personal information. Data collection will be performed using paper CRFs, which will be handed over to an authorized research assistant on the same day as each completed evaluation. The data collected will be converted into electronic format and securely stored on an encrypted hard drive.

### Statistical analysis

All primary and secondary analyses will be conducted on an intention-to-treat (ITT) basis. Modified ITT analysis included all randomized participants who completed at least 8 weeks of the intervention. Primary analyses will be conducted using multiple imputation methods for missing observations at baseline, post intervention, and at follow-up, assuming missing data are missing at random. Prespecified sensitivity analyses will be conducted for all participants using complete-case data at each time point.

Continuous data will be presented as mean ± SD or median ± quartile interval, while enumeration data will be presented as numbers and percentages. Between-group differences in demographic and baseline variables, as well as assessment variables, will be assessed using a chi-square test or the Fisher exact test for categorical variables and a one-way analysis of variance (ANOVA) or the Kruskal-Wallis test for continuous variables as appropriate. Intervention effects on primary and secondary continuous outcome measures will be compared by means of mixed repeated-measures analysis of variance, with and without adjustment for baseline and time-varying covariates (e.g., age, sex, and Hoehn and Yahr stage). Pairwise comparisons between the Yijinjing group and the two other groups will be conducted only if the omnibus F-test statistics indicated that the null hypothesis should be rejected. The primary analysis will to determine whether Yijinjing training improved the MoCA and UPDRS-III score compared with brisk walking training and control at 12 weeks. These continuous outcomes will be assessed by the 1-way analysis of variance model at 12 and 16 weeks. All statistical analyses will be conducted using SPSS software, version 24 (IBM). *p* value < 0.05 will be considered statistically significant. An independent statistician will carry out all statistical analyses.

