**Assessments**					
MoCA^*^		**×**		**×**	**×**
UPDRS-III^*^		**×**		**×**	**×**
BBS^*^		**×**		**×**	**×**
TMT^*^		**×**		**×**	**×**
6MWT^*^		**×**		**×**	**×**
PSQT^*^		**×**		**×**	**×**
PDQ-39^*^		**×**		**×**	**×**
fNIRS^*^		**×**		**×**	**×**
Adverse events		**×**	**×**	**×**	**×**

^*^Descriptive information includes the personal general data, vital signs, history of present illness, clinical symptoms and signs, medical history, medication history and neurological examination. “**×**” means the item will be completed. MoCA, Montreal Cognitive Assessment; UPDRS-III, Unified Parkinson’s Disease Rating Scale motor section; BBS, the Berg Balance Scale; TMT, Trail Making Test; 6MWT, 6-MinuteWalk Test; PSQI, Pittsburgh sleep quality index; PDQ-39, Parkinson’s disease questionnaire 39; fNIRS, functional near-infrared spectroscopy.

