### Sample size calculation

The design of this study is novel. According to the trial design and previous literature assessment, the sample size will be calculated based on hypothetical changes in MoCA score (28) or UPDRS motor score (10) at week 12. With a power of 90% and an alpha of 5% (two-sided). The SD from our feasibility study is used and our power calculation considered our planned analysis method, by means of an analysis of covariance (ANCOVA) in which baseline measurements served as a covariates, reducing the needed sample size (29). we calculated the minimum sample size (effect size = 0.3) in MoCA score (SD = 2.07, Difference = 1.8) to be 28 participants per group and UPDRS motor score (SD = 2.55, Difference = 1.9) to be 38 through PASS software (version 15.0.5). Therefore, With a 15% dropout rate considered, a total sample size of 135 participants will be necessary.

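### The adjusted effect models may include time-varying covariates; if a post-randomisation Hoehn and Yahr stage is entered, they no longer estimate the total treatment effect

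*Protocol article*

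**What the plan says.** All of the following is in the protocol article.

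- **Model and scope (Statistical analysis).** "Intervention effects on primary and secondary continuous outcome measures will be compared by means of mixed repeated-measures analysis of variance". The sentence continues "with and without adjustment for baseline and time-varying covariates (e.g., age, sex, and Hoehn and Yahr stage". The covariates form one undivided list of examples, and neither the adjusted nor the unadjusted version is given precedence.
- **Second model (Statistical analysis).** After stating the 12-week question on MoCA and UPDRS-III, the section adds: "These continuous outcomes will be assessed by the 1-way analysis of variance model at 12 and 16 weeks". No covariates are mentioned there.
- **Primary outcomes (Primary outcome).** "Cognitive and motor functions will be measured using the MoCA and UPDRS assessments, respectively", and "UPDRS-III is the motor section of UPDRS".
- **Hoehn and Yahr stage elsewhere.** It appears as an eligibility limit, "Hoehn Yahr grade of I–III" (Inclusion criteria), and is not listed as an outcome. Table 1 has no row for it. The nearest item is the descriptive information, which includes "medical history, medication history and neurological examination" and is ticked once, at baseline.
- **Sample size calculation.** The analysis described there is an analysis of covariance with baseline measurements as covariates.
- **Quality control.** Participants' medication is recorded throughout the trial.

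**The concern.** A covariate measured before randomisation cannot be affected by the assigned arm, so adjusting for it leaves the randomised comparison intact. A covariate measured afterwards has no such protection. The trial's hypothesis is that Yijinjing improves motor function. If it does, a later Hoehn and Yahr stage may itself be partly a result of treatment. A model that holds stage constant then estimates only the part of the UPDRS-III effect that stage does not reflect. It also compares participants who are alike on something that happened after allocation.

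The stated question is whether training improves MoCA and UPDRS-III at 12 weeks, which is a total effect. An adjusted result answering a narrower question would stand beside the unadjusted one with no rule for which prevails, and a difference between the two could be misread as fragility of the finding.

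**Working it through.** **1. Which listed examples can vary over time?** Sex is fixed. Age advances equally in every arm over 16 weeks, so it carries no time-varying information about treatment. Stage is the only listed example that could vary informatively. Because the list is given as examples, unlisted variables could also enter. Medication is one, since it is recorded throughout.

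**2. Is a later stage value available?** Table 1 schedules none. Two readings remain:

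| Reading | Consequence |
|---|---|
| Stage is a baseline covariate | Adjustment for stage is sound, but time-varying then has no meaningful listed example and admits unspecified variables |
| Stage is time-varying | The adjusted estimate is open to bias, and the covariate is not in the schedule |

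The wording needs changing under either.

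**3. The plan's own figures.** These are reproduced to fix the planned effect; the point does not depend on them. Inputs are from Sample size calculation: "With a power of 90% and an alpha of 5% (two-sided"; MoCA difference 1.8, SD 2.07; UPDRS-III difference 1.9, SD 2.55; dropout 15%. Using n per group = 2(1.960 + 1.282)² × (SD/difference)², where 2(1.960 + 1.282)² ≈ 21.02:

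- MoCA: 21.02 × (2.07/1.8)² = 21.02 × 1.3225 ≈ 27.8, so 28.
- UPDRS-III: 21.02 × (2.55/1.9)² = 21.02 × 1.801 ≈ 37.9, so 38.
- 38/0.85 = 44.7, so 45 per group, and 3 × 45 = 135.

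All three stated figures reproduce.

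**4. Direction of the bias, under assumptions.** Let treatment improve the later covariate by *a* standard deviations, and let the covariate and outcome correlate at ρ within arms. In a linear model the adjusted effect is

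adjusted effect = difference − ρ × a × SD.

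Neither *a* nor ρ is in the article. With the planned 1.9 points and SD 2.55, assumed values give:

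| Assumed *a* | Adjusted effect, ρ = 0.3 | Adjusted effect, ρ = 0.7 | Share removed |
|---|---|---|---|
| 0 | 1.90 | 1.90 | 0% |
| 0.1 | 1.82 | 1.72 | 4% to 9% |
| 0.3 | 1.67 | 1.36 | 12% to 28% |
| 0.5 | 1.52 | 1.01 | 20% to 47% |

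For example, 1.9 − 0.7 × 0.5 × 2.55 = 1.9 − 0.89 = 1.01. A simulation of the same model agreed with the formula to within 0.03 points. The table shows direction and dependence on the assumptions. It does not estimate the bias in this trial.

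**The case against.** A reader might infer that the plan adjusts its effect models for post-baseline Hoehn and Yahr stage and so removes part of the treatment effect. The article does not support that. The list does not label stage as time-varying, its two companions are plainly baseline characteristics, and no later stage is scheduled. A baseline value is at least as compatible with the text.

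A reader might also infer that every effect estimate is compromised. It is not: each mixed model is also run without adjustment, and the one-way analysis of variance named for 12 and 16 weeks has no covariates. Nothing makes the adjusted version primary.

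Nor can the point be turned into a loss of power. That would need the share of the 1.9 points carried by stage, which the article does not give. Adjusting for a covariate correlated with the outcome also lowers the residual SD, so a calculation that keeps 2.55 would be wrong. Finally, it is not established that a coarse ordinal stage would move within 12 to 16 weeks; if it does not, nothing is removed.

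It can be added that a condensed article commonly leaves covariate definitions to the analysis plan. That excuses missing detail. It does not cover the term time-varying, which is a stated rule that permits covariates measured after randomisation.

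These objections stand as limits on how far the point reaches. They do not defend the wording: running an unadjusted model alongside does not make an adjusted model with a post-randomisation covariate valid.

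**Conclusion.** The point holds conditionally. The plan permits time-varying covariates in the adjusted models for primary and secondary outcomes, without defining them, and with Hoehn and Yahr stage among the examples. If a post-randomisation stage, or another variable affected by treatment such as medication, is entered, the adjusted estimate does not target the total effect and could be biased. For UPDRS-III and stage the bias would usually be toward no effect, assuming treatment moves both in the same direction and they correlate positively within arms. For MoCA, or for medication as the covariate, the article gives no basis for stating a direction.

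No size can be attached to this from the article, and no power figure should be. The sample size and the unadjusted analyses are untouched.

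**What to change.** Delete time-varying from the sentence on covariate adjustment. State that adjusted models use only covariates measured before randomisation: baseline outcome score, age, sex and baseline Hoehn and Yahr stage. The baseline score should enter as a covariate where the repeated measures are the 12-week and follow-up values, so that it is not used twice.

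This agrees with the baseline-covariate analysis of covariance described under Sample size calculation. The cost is a wording change. Age and stage are established at eligibility, and sex and the outcome scores are collected at baseline, so no visit, measurement or participant is added. If the team wishes to examine stage or medication over time, that belongs in a separately labelled mechanistic analysis, not among the effect estimates.
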